# A single-center, randomized, parallel design study to evaluate the efficacy of donepezil in improving visuospatial abilities in patients with mild cognitive impairment using eye-tracker: the COG-EYE study protocol for a phase II trial

**DOI:** 10.1186/s13063-022-06781-0

**Published:** 2022-09-27

**Keywords:** Mild cognitive impairment, Donepezil, Cholinesterase inhibitors, Visuospatial dysfunction, Eye-tracking, Digital pen

## Abstract

**Background:**

Cholinesterase inhibitors (ChEIs) decrease long-term cognitive decline in patients with Alzheimer’s disease (AD); however, there is little evidence that ChEIs affect cognitive test scores in patients with mild cognitive impairment (MCI). Conventional endpoints, such as cognitive tests or clinical rating scores, may lack the sensitivity to subtle treatment effects in participants with MCI. Therefore, there is an immediate need to refocus on direct physiological assessments to detect the effects of ChEIs in patients with MCI due to AD.

**Methods:**

We propose a randomized controlled trial to evaluate the effect of donepezil, a ChEI, on patients with MCI due to AD. We plan to recruit 78 participants (39 in each arm) with MCI who had amyloid positron emission tomography (PET)-positive results for this open-label study. To evaluate subtle differences, we will measure eye-tracking metrics and digital pen data while participants perform the simplified Rey Complex Figure (RCFT) and clock drawing tests. The primary outcome is a change in the ratio of the number of fixations (working space/perceptual space) performed using the simplified RCFT, from baseline to 12 weeks, as assessed using eye-tracking metrics. The secondary outcomes are changes in general cognition, clinical severity, activities of daily living, and visuospatial function assessed using standard rating scores and digital pen data. The analyses of the primary and secondary outcomes will be based on the difference in changes during follow-up between the donepezil and control groups using the *t*-test or Mann–Whitney *U* test, as well as adjusting for baseline values.

**Discussion:**

This study is designed to determine whether eye-tracking metrics can detect the effect of donepezil on visuospatial dysfunction more sensitively in patients with MCI. It is expected that multimodal data, such as eye-tracking and digital pen data, may provide helpful biomarkers for identifying subtle changes that are difficult to measure using conventional methods.

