## Introduction

### Background and rationale {6a}

Mild cognitive impairment (MCI) and dementia are not separate diseases, but on the same disease course. According to the amyloid/tau/neurodegeneration (ATN) classification, MCI with Alzheimer’s disease (AD) biomarkers is defined as a clinical stage of Alzheimer’s continuum [1]. Based on the need for early detection and treatment, disease-modifying treatment has recently been approved for the treatment of MCI or stage of AD with mild dementia [2]. However, since patients who can be administered this new drug are still limited in number, there is an immediate need to refocus on the use of cholinesterase inhibitors (ChEIs), which have been approved for dementia.

A previous study showed that ChEIs decreased long-term cognitive decline and the risk of death in AD dementia [3]. However, there is very little evidence that ChEIs affect cognitive test scores in MCI [4, 5]. A recent meta-analysis showed that ChEIs have only a slight effect in the treatment of MCI [6]. The limitations of previous trials and meta-analysis results are as follows. First, the MCI participants were not diagnosed based on AD biomarkers. It is possible that there was an effect of ChEIs on MCI due to AD, but it might be attenuated in other MCI with heterogeneous causes. Second, cognitive tests or clinical rating scores, which were used as primary outcomes, were not sensitive to subtle changes in participants with MCI. Therefore, it is necessary to consider using a surrogate marker that can reflect the effect of ChEIs more sensitively than cognitive tests or clinical rating score endpoints.

We propose a randomized controlled trial to evaluate the effect of donepezil, a ChEI, in patients with MCI due to AD who have amyloid positron emission tomography (PET)-positive results. To evaluate the subtle differences, we propose measuring eye tracking metrics as a surrogate marker. Several previous studies have shown that AD-related eye movement changes reflect underlying cognitive processes [7].

We hypothesized that:

1. Treatment with donepezil will be beneficial for visuospatial dysfunction in patients with amyloid PET-positive MCI.

2. Eye-tracking metrics and digital pen data may offer biomarkers to evaluate subtle improvements in visuospatial abilities.

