## Objectives {7}

### Primary

1. To evaluate whether the use of donepezil benefits visuospatial function in patients with amyloid PET-positive MCI by assessing eye-tracking metrics involves a simplified Rey-Osterrieth Complex Figure test (RCFT).

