We modified the original RCFT to a simpler version and validated our simplified RCFT against the original RCFT in a previous study [13]. To evaluate subtle differences, we will measure eye-tracking metrics and digital pen data during copying and determine whether these digital data are useful as surrogate markers for evaluating visuospatial dysfunction. CDT is one of the most widely used screening tests for AD, and digital CDT has recently been introduced [14, 15]. We will also measure eye-tracking metrics and digital pen data while participants perform the digital CDT (Fig. 3).

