## Statistical methods

### Statistical methods for primary and secondary outcomes {20a}

As the trial has a parallel design, all analyses will be performed for comparison between the donepezil and control groups. The primary outcome will be analyzed using the two-sample *t*-test, the continuous secondary outcome will be analyzed using the two-sample *t*-test or Mann–Whitney *U* test according to normality, and the ordinal secondary outcome will be analyzed using the Mann–Whitney *U* test. An analysis adjusting for the baseline value will also be performed for each outcome. All results will be presented as mean, median, standard deviation, interquartile range, minimum maximum, and 95% confidence intervals. Sensitivity analyses will be performed to report the robustness of the data.

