### Methods for additional analyses (e.g. subgroup analyses) {20b}

Subgroup analysis will be performed based on the age and education groups. In addition, we will perform a correlation analysis between eye-tracking metrics and cognitive test scores.

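### The abstract says the study is designed to determine whether eye-tracking detects the donepezil effect more sensitively, but no stated analysis compares the treatment effect between measures.

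*Protocol article*

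**What the plan says.** The comparative aim is in the abstract's Discussion, where the study is "designed to determine whether eye-tracking metrics can detect the effect of donepezil on visuospatial dysfunction more sensitively". The comparator is supplied elsewhere. The abstract's Background says: "Conventional endpoints, such as cognitive tests or clinical rating scores, may lack the sensitivity to subtle treatment effects in participants with MCI". Background and rationale {6a} argues for "using a surrogate marker that can reflect the effect of ChEIs more sensitively than cognitive tests or clinical rating score endpoints". Section {6b} gives the same reason for choosing eye-tracking and digital pen data.

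The primary objective in {7} is narrower: "To evaluate whether the use of donepezil benefits visuospatial function in patients with amyloid PET-positive MCI by assessing eye-tracking metrics". The secondary objectives ask about the effect of donepezil on each score, and whether digital pen data and clock-drawing eye metrics can serve as biomarkers. None of them compares one measure with another.

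On analysis, {20a} says "all analyses will be performed for comparison between the donepezil and control groups", with a t-test or Mann–Whitney U test for each outcome, and adds: "An analysis adjusting for the baseline value will also be performed for each outcome". The one stated analysis that links two measures is in {20b}: "we will perform a correlation analysis between eye-tracking metrics and cognitive test scores".

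**The concern.** Whether one measure is more sensitive to treatment than another is a question about the difference between two treatment effects, put on a common scale and estimated in the same patients. A between-arm test on each outcome estimates the two effects separately and says nothing formal about their difference. A correlation describes association: two measures can correlate strongly and respond unequally to treatment, or respond equally and be nearly uncorrelated.

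At stake is the conclusion about the method, not the one about the drug. Section {6b} expects that significant change in the scores may be hard to see over 12 weeks. A result in which the fixation ratio reaches significance and the scores do not is therefore quite possible, and could easily be read as proof of greater sensitivity. That pattern also arises when the two measures are equally sensitive.

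**Working it through.** **The plan's own figure.** Inputs from Sample size {14}: standardised effect 0.8, two-sided alpha 0.05, power 90%, two-sample t-test, 12% attrition. The noncentral t calculation gives n = 33.8, so 34 per group, with power 90.2%. Attrition: 34 / 0.88 = 38.6, so 39 per group and 78 in total. The stated size reproduces and is not in dispute. It covers the between-arm test on the fixation ratio only.

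**What the stated analyses return.** For each outcome, {20a} gives an estimated arm difference with a 95% interval and a test. {20b} gives a correlation coefficient. The quantity that the abstract's sentence needs is D = d(ratio) − d(score), the difference between two standardised effects in the same participants. Neither section estimates D.

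**How often equal measures look unequal.** Assume two outcomes with the same true effect d, 34 per arm, both tested by t-test. The documents give no correlation between measures, so it is varied. At zero correlation, the chance that the ratio is significant and the score is not is power × (1 − power):
- d = 0.5: power 0.529, so 0.529 × 0.471 = 0.249
- d = 0.8: power 0.902, so 0.902 × 0.098 = 0.088

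Simulation (40,000 trials) gives:

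| True d for both | Correlation 0 | 0.3 | 0.5 |
|---|---|---|---|
| 0.5 | 0.247 | 0.202 | 0.165 |
| 0.8 | 0.088 | 0.079 | 0.067 |

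A separate run of 20,000 trials agrees to within 0.002.

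**How precisely D could be estimated.** To first order, SE(D) = √[2(1 − ρ) × 2/34]. This gives 0.34, 0.29 and 0.24 for ρ = 0, 0.3 and 0.5. The simulated values are 0.35, 0.30 and 0.25 at d = 0.5, and 0.36, 0.31 and 0.26 at d = 0.8. The 95% half-width therefore runs from 1.96 × 0.25 = 0.49 to 1.96 × 0.36 = 0.71 SD.

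**Power to show a difference.** With effect (d1 − d2)/√[2(1 − ρ)] and 34 per arm, and d1 = 0.8 for the ratio:

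| Score effect d2 | ρ = 0 | 0.3 | 0.5 | 0.7 |
|---|---|---|---|---|
| 0.3 (lower end of the range cited in {14}) | 30% | 40% | 53% | 75% |
| 0.5 | 14% | 18% | 23% | 35% |

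**The case against.** The strongest reply is that comparative sensitivity is not an objective of the trial. None of the numbered objectives compares measures, and the main Discussion restates the aim as whether donepezil improves visuospatial function. The comparative wording sits in the abstract and in the reasons for choosing the endpoint. This stands, and it limits the point: no numbered aim is left unanswerable. It does not remove the point, because the abstract says outright what the study is designed to determine, and {20a} and {20b} then list analyses that do not determine it. That is a mismatch between two stated things, not a detail left to a fuller document.

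Three stronger readings are tempting and are not supported:
- A reader might infer that the claim would have to rest on comparing p-values. The article does not say how it would be judged. {20a} promises means, standard deviations and 95% intervals, so effects could be set side by side informally. No formal comparison is stated.
- A reader might infer that the aim in {11a}, to "determine whether these digital data are useful as surrogate markers for evaluating visuospatial dysfunction", fails for the same reason. That sentence concerns usefulness. A marker can be useful without being more sensitive than a score, so the wording can stay.
- A reader might infer that the {20b} correlation pools levels across arms. The text does not say whether levels or changes are used, or whether arms are pooled, and such detail may properly sit in the analysis plan.

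It is also fair to say that at the protocol's own planning effect the misleading pattern is uncommon.

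**Conclusion.** The mismatch is real and worth correcting. The stated analyses can show a donepezil effect on the fixation ratio. They cannot show that the ratio is more sensitive than conventional scores. The primary test, the sample size and the numbered objectives are unaffected.

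If the two measures were equally sensitive, the pattern most likely to be misread would occur in about 17 to 25% of trials at a common effect of 0.5 SD and 7 to 9% at 0.8 SD. These rates rest on assumed equal effects, assumed correlations of 0.5 to 0, 34 completers per arm and t-tests on both outcomes; an outcome analysed by Mann–Whitney U would differ somewhat. They illustrate the risk and do not predict this trial's result.

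**What to change.** Add one exploratory analysis to {20b}. In the same participants, estimate the difference between the baseline-adjusted standardised effect on the fixation ratio and that on VOSP, both as change to 12 weeks, with a paired bootstrap 95% interval. VOSP is the natural single comparator because the abstract's sentence concerns visuospatial dysfunction and VOSP is the conventional visuospatial score. Naming only one also avoids several comparisons without a decision rule. State beforehand which direction of the ratio counts as improvement, since the article does not say and the sign of the difference depends on it.

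Claim greater sensitivity only if the interval lies above zero. Otherwise limit the abstract's sentence to a donepezil effect on the fixation ratio, in line with the primary objective and the main Discussion.

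The cost is a little more analysis on data already collected. The drawback is precision: with a half-width of about 0.5 to 0.7 SD and the power shown above, the claim may well not be reached, which is why the comparison should be labelled exploratory.

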**Trial registration:**

Clinical Research Information Service, Republic of Korea (CRIS, cris.nih.go.kr) KCT0006236. Registered on June 10, 2021.

## Administrative information

Note: the numbers in curly brackets in this protocol refer to SPIRIT checklist item numbers. The order of the items has been modified to group similar items (see http://www.equator-network.org/reporting-guidelines/spirit-2013-statement-defining-standard-protocol-items-for-clinical-trials/).

## Introduction

### Background and rationale {6a}

Mild cognitive impairment (MCI) and dementia are not separate diseases, but on the same disease course. According to the amyloid/tau/neurodegeneration (ATN) classification, MCI with Alzheimer’s disease (AD) biomarkers is defined as a clinical stage of Alzheimer’s continuum [1]. Based on the need for early detection and treatment, disease-modifying treatment has recently been approved for the treatment of MCI or stage of AD with mild dementia [2]. However, since patients who can be administered this new drug are still limited in number, there is an immediate need to refocus on the use of cholinesterase inhibitors (ChEIs), which have been approved for dementia.

A previous study showed that ChEIs decreased long-term cognitive decline and the risk of death in AD dementia [3]. However, there is very little evidence that ChEIs affect cognitive test scores in MCI [4, 5]. A recent meta-analysis showed that ChEIs have only a slight effect in the treatment of MCI [6]. The limitations of previous trials and meta-analysis results are as follows. First, the MCI participants were not diagnosed based on AD biomarkers. It is possible that there was an effect of ChEIs on MCI due to AD, but it might be attenuated in other MCI with heterogeneous causes. Second, cognitive tests or clinical rating scores, which were used as primary outcomes, were not sensitive to subtle changes in participants with MCI. Therefore, it is necessary to consider using a surrogate marker that can reflect the effect of ChEIs more sensitively than cognitive tests or clinical rating score endpoints.

We propose a randomized controlled trial to evaluate the effect of donepezil, a ChEI, in patients with MCI due to AD who have amyloid positron emission tomography (PET)-positive results. To evaluate the subtle differences, we propose measuring eye tracking metrics as a surrogate marker. Several previous studies have shown that AD-related eye movement changes reflect underlying cognitive processes [7].

We hypothesized that:

1. Treatment with donepezil will be beneficial for visuospatial dysfunction in patients with amyloid PET-positive MCI.

2. Eye-tracking metrics and digital pen data may offer biomarkers to evaluate subtle improvements in visuospatial abilities.

## Objectives {7}

### Primary

1. To evaluate whether the use of donepezil benefits visuospatial function in patients with amyloid PET-positive MCI by assessing eye-tracking metrics involves a simplified Rey-Osterrieth Complex Figure test (RCFT).

### Secondary

2. To evaluate whether donepezil improves general cognition in patients with amyloid PET-positive MCI by assessing Mini-Mental State Examination (MMSE) scores.3. To evaluate whether donepezil is associated with changes in clinical severity in patients with amyloid PET-positive MCI by assessing Clinical Dementia Rating (CDR) scores.4. To determine whether donepezil is associated with cognitive function in patients with amyloid PET-positive MCI by assessing Global Deterioration Scale (GDS) scores.5. To determine whether donepezil correlates with changes in activities of daily living (ADL) in patients with amyloid PET-positive MCI by assessing Seoul-Instrumental Activities of Daily Living (S-IADL) scores.6. To evaluate whether donepezil improves visuospatial function in patients with amyloid PET-positive MCI by assessing Visual Object and Space Perception Battery (VOSP) scores.7. To evaluate whether digital pen data can be used as a biomarker to find nuanced changes in visuospatial function.8. To evaluate whether eye-tracking metrics in can be used as a biomarker to find nuanced changes in visuospatial function involves a clock drawing test (CDT).

## Trial design {8}

The COG-EYE is a randomized, open-label, parallel design, superiority trial with a 1:1 allocation ratio to evaluate the efficacy of donepezil in improving visuospatial abilities in patients with MCI.

## Methods: participants, interventions, and outcomes

### Study setting {9}

This study will be conducted in a single center, Biomedical Research Institute, Jeonbuk National University Hospital.

### Eligibility criteria {10}

Inclusion criteria:

Participant is willing and able to give informed consent for participation in the trial.

The participant may enter the trial if all of the following apply.1. Male and female, aged ≥ 60 years and < 90 years.2. Diagnosis of MCI according to Peterson Criteria [8]3. More than 6 years of education (more than elementary school graduation).4. Normal or corrected-to normal visual acuity (visual acuity ≥ 0.3).5. Completion of a dementia work-up including neuropsychological tests, blood tests, and brain magnetic resonance imaging (MRI).6. 18F-flutemetamol PET scan-positive based on the visual assessment system [9]7. MMSE test score of 19 or above.

Exclusion criteria:

The participant may not enter the trial if ANY of the following apply.1. A severe neurological condition other than AD is the cause of cognitive impairment (for example, territorial infarction, intracranial hemorrhage, brain tumor, and hydrocephalus).2. Severe white matter hyperintensities (WMH) on brain MRI (defined as a cap or a band ≥ 10 mm, as well as a deep white matter lesion ≥ 25 mm, as modified from the Fazekas ischemia criteria ref).3. Use of ChEIs (donepezil, rivastigmine, and galantamine) or N-methyl-D-aspartate (NMDA) receptor antagonists (memantine) within the previous 3 months.4. Other sever medical condition (for example, renal failure and liver failure) within last 3 months.5. Major depression or other significant psychiatric diseases.6. Malignant tumorous disease (cancer) within the last 3 years, except for cervical intraepithelial neoplasia (CIN) and non-melanoma skin cancer.7. History of cerebrovascular surgery, such as brain surgery or carotid artery surgery.8. Difficulty breathing when sitting.9. Impairment in memory, speech, or problem-solving ability for more than 2 h after a heart attack.10. Hospitalization for mental or emotional problems within the last 5 years.11. History of drug abuse within the last 5 years.12. History of treatment for alcoholism within the past 5 years.13. Lost consciousness for more than 1 h due to causes other than general anesthesia.14. History of hospitalization due to head trauma.15. Severe vision loss (visual acuity < 0.3).16. Difficulty in understanding conversations due to hearing impairment even with hearing aids.17. If the investigator determines that participants are at risk because of participation in the trial, which may influence the result of the trial or the participant’s ability to participate in the trial.18. Currently enrolled in another clinical trial or using any investigational drug or device within 30 days or 5 × the half-life, whichever is longer, preceding informed consent.

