**Fig. 2 Fig2:**
[figure not shown]
COG-EYE schedule of enrolment, interventions, and assessments**.** CDR, Clinical Dementia Rating; ECG, echocardiography; GDS, Global Deterioration Scale; MMSE, Mini-Mental State Examination; MRI, magnetic resonance imaging; PET, positron emission tomography; S-IADL, Seoul-Instrumental Activities of Daily Living; TC, telephone consultation; V, visit; VOSP, visual object and space perception battery

During the screening visit, blood samples (for analyses of thyroid function, folic acid, and vitamin b12; syphilis screening; and apolipoprotein E genotyping), echocardiography (ECG), neuropsychological test battery, brain MRI, and amyloid PET will be collected. These results are needed to screen for other causes of cognitive impairment and to only recruit patients with MCI in the Alzheimer’s continuum.

Allocation will occur after baseline screening. Donepezil will be packed with clear dosing instructions and schedule. At visit 1, detailed baseline assessments will be required of all participants. Then, participants allocated to the donepezil group will be instructed to consume a dose of 5 mg once daily for the first 4 weeks. The participants allocated to the control group will not be administered donepezil during the study period. At visit 2, follow-up assessments of the measures of efficacy, except for VOSP, and detailed reporting of potential adverse effects will be required of all participants. Participants allocated to the donepezil group will then be instructed to increase the dose to 10 mg once daily for the next 8 weeks. At visit 3, follow-up assessments, including all measures of efficacy performed at baseline, and detailed reporting of potential adverse effects will be required of all participants.

V1, V2, and V3 measurements will be acquired with the following means.1. Eye-tracking metrics during the simplified RCFT and CDT on a digital tablet.2. MMSE3. CDR4. GDS5. S-IADL6. VOSP (VOSP is not performed at V2).7. Digital pen data during simplified RCFT copying test on digital tablet [13]

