### Outcomes {12}

#### Primary

1. Changes in the ratio of the number of fixations between the two AOIs (working space/perceptual space) performed by the simplified RCFT from baseline to 12 weeks (Fig. 3).

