### Plans to promote participant retention and complete follow-up {18b}

Participants will be in close contact with each other. There will be scheduled safety checks and frequent contact with the research staff as per the participants’ wish. All randomized participant data will be included in the analysis. If participants withdraw from the study at any stage, they will be asked whether their data accumulated at the point of withdrawal could be included.

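### No stated step before randomisation shows that a participant can be eye-tracked, so failure to record the primary endpoint may first come to light after open allocation

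*Protocol article*

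**What the plan says.** - **Endpoint.** Outcomes {12} defines the primary outcome, with time counted in weeks, as "Changes in the ratio of the number of fixations between the two AOIs (working space/perceptual space) performed by the simplified RCFT from baseline to 12". Each participant needs a usable recording at both times.
- **Ocular eligibility.** Eligibility criteria {10} lists 7 inclusion and 18 exclusion criteria. Those that specifically concern the eyes are inclusion 4, "Normal or corrected-to normal visual acuity (visual acuity ≥ 0.3"), and its mirror, exclusion 15, "Severe vision loss (visual acuity < 0.3").
- **Discretionary exclusion.** Exclusion 17 lets the investigator exclude a participant judged to be at risk from taking part, "which may influence the result of the trial or the participant’s ability to participate in the trial". It names no tracking test.
- **Screening.** Intervention description {11a}, in the text under Fig. 2, lists blood samples, ECG, "neuropsychological test battery, brain MRI, and amyloid PET will be collected". Eye-tracking is not among them.
- **Order of events.** The same text continues: "Allocation will occur after baseline screening". Visit 1 comes next: "At visit 1, detailed baseline assessments will be required of all participants". Dosing instructions to the donepezil arm follow. Eye-tracking is listed for V1, V2 and V3. Implementation {16c} also puts allocation after baseline screening, and Concealment mechanism {16b} puts it after general screening.
- **Blinding.** Sequence generation {16a} and the blinding sections make the trial open after assignment. {16a} offers the choice of an eye-tracking outcome as the protection against open-label bias.
- **Analysis.** Section {18b} states: "All randomized participant data will be included in the analysis". Section {20a} plans a two-sample t-test for the primary outcome. Section {20c} says that missing data will be sought and filled in where possible.

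**The concern.** Acuity of 0.3 or better does not show that a person's gaze can be calibrated and recorded. Someone aged 60 to 89 with adequate acuity but, say, marked ptosis or nystagmus could meet every specific criterion and still give no usable recording. As the narrative is ordered, no scheduled step would reveal this before the arm is assigned.

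Three things are at stake:

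1. A randomised participant without a usable baseline recording has no change score, and the recording cannot be recovered afterwards by asking for it.
2. Whether a recording is usable would first be decided by staff who know the arm, in a trial that relies on this endpoint to limit open-label bias.
3. The places lost may come out of an attrition allowance that was not stated to cover recording failure.

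**Working it through.** **Order of events.** Setting the sections side by side gives: screening (no eye-tracking listed), then open allocation, then V1 baseline assessments including the first eye-tracking, then the first dose. The gap lies between the second and third steps. Because V1 precedes dosing, a failure to track at V1 cannot be an effect of donepezil. It can only be judged with knowledge of the arm.

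**Inputs from Sample size {14}.** Effect size d = 0.8, two-sided alpha 0.05, target power 90%, 34 per group, 12% attrition, 39 per group (78 in total).

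**Reproducing the plan.** Power comes from the noncentral t distribution with 2n − 2 degrees of freedom and noncentrality d·√(n/2).

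- n = 33 per group: power 89.3%.
- n = 34 per group: noncentrality 0.8·√17 = 3.30, power 90.15%. So 34 is the smallest size that reaches 90%.
- Attrition: 34 / 0.88 = 38.6, rounded up to 39 per group, 78 in total.

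The plan's figures are reproduced.

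**Effect of tracking failure.** The documents give no failure rate. Let u be the assumed share with no usable recording, on top of the 12%. Evaluable participants per group are 39 × 0.88 × (1 − u), rounded down. Randomised participants needed per group to keep 34 evaluable are 34 / (0.88 × (1 − u)), rounded up.

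| u (assumed) | Evaluable per group | Power at d = 0.8 | Needed per group to keep 34 |
|---|---|---|---|
| 0% | 34.32 → 34 | 90.15% | 39 |
| 5% | 32.60 → 32 | 88.3% | 41 |
| 10% | 30.89 → 30 | 86.1% | 43 |
| 15% | 29.17 → 29 | 84.9% | 46 |

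If tracking failures are already counted in the 12%, the first row applies and nothing is lost. Section {14} does not break the 12% down by cause, so either reading is possible.

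**What cannot be computed.** Any bias from judging usability with the arm known depends on how that judgement is made, and the documents do not describe it.

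**The case against.** The case on the other side has several parts.

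- **Condensed article.** Calibration rules and recording-quality thresholds may stand in the full protocol, and the visit schedule is in a figure that is not shown. This stands as a limit on the point: allocation before V1 tracking is the natural reading of the narrative, not an outright statement. It does not remove the point, because the eligibility list reads as complete and the screening content is spelled out.
- **Exclusion 17.** An investigator might use it to keep out a person who plainly cannot be tracked. That is fair, but its wording is tied to risk, and it helps only if the problem is known before allocation.
- **Bias.** V1 precedes dosing, so loss at V1 would differ between arms only if quality were judged differently by arm. Nothing suggests that staff would do so. This stands: the bias is a possibility that the design leaves open, not a demonstrated fault.
- **Size.** The failure rate is an assumption, and the power loss is modest even at 15%.

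Two stronger readings are tempting. A reader might infer that section {18b} is contradicted. It is not: no text excludes untrackable participants, and the promise is only hard to keep for someone with no recording. A reader might also infer that a visual field defect or restricted vertical gaze biases the result, because the two areas are the upper and lower halves of the display. The endpoint is a within-person change compared between randomised arms. A stable defect is present at both recordings and is allocated at random, so it largely cancels and at most adds noise.

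**Conclusion.** The point holds as a design weakness that is cheap to repair. As written, a participant can be randomised openly before any stated step shows that the primary endpoint can be recorded for that person.

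The effect on power runs from none, if failures sit within the 12%, to a fall from about 90% to about 85% if a further 15% fail. The 5% to 15% range is assumed. The calculation also assumes equal loss in both arms and takes the plan's effect size of 0.8 as given. The main reason to act is that a usability judgement on the primary endpoint should not first be made with the arm known. That consequence cannot be quantified from the documents. The conclusion rests on the narrative order in {11a} and would fall away if the schedule figure or full protocol places a valid recording before allocation.

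**What to change.** Obtain the V1 baseline eye-tracking recording before the allocation is opened, or add a calibration and short gaze recording at screening. Make a valid recording, against a quality threshold fixed in advance, a condition of randomisation. Apply the same threshold to the later recordings irrespective of arm. A pre-randomisation check cannot prevent failures that first arise at week 12, so the common threshold is needed as well.

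The equipment, trained staff and baseline assessment are already part of the trial at its single centre. The costs are:

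- **More screen failures.** At the assumed rates, randomising 78 would need 78/0.95, 78/0.90 or 78/0.85 otherwise eligible people, that is 83, 87 or 92, or 5 to 14 extra.
- **A narrower population.** Results would apply to patients who can be tracked, who are the only ones able to supply the primary outcome.
- **An amendment during recruitment.** The first participant was recruited in July 2021 and recruitment runs to December 2023. The rule would apply only to participants not yet randomised, and the report should say from when it applied.
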